## Abstract

**Introduction:**

Shoulder osteoarthritis most commonly affects older adults, causing pain, reduced function and quality of life. Total shoulder replacements (TSRs) are indicated once other non-surgical options no longer provide adequate pain relief. Two main types of TSRs are widely used: anatomic TSR (aTSR) and reverse TSR (rTSR). It is not clear whether one TSR type provides better short- or long-term outcomes for patients, and which, if either, is more cost-effective for the National Health Service (NHS).

**Methods and analysis:**

RAPSODI-UK is a multi-centre, pragmatic, two-parallel arm, superiority randomised controlled trial comparing the clinical- and cost-effectiveness of aTSR versus rTSR for adults aged 60+ with a primary diagnosis of osteoarthritis, an intact rotator cuff and bone stock suitable for TSR. Participants in both arms of the trial will receive usual post-operative rehabilitation. We aim to recruit 430 participants from approximately 28 NHS sites across the UK. The primary outcome is the Shoulder Pain and Disability Index (SPADI) at 2 years post-randomisation. Outcomes will be collected at 3, 6, 12, 18 and 24 months after randomisation. Secondary outcomes include the pain and function subscales of the SPADI, the Oxford Shoulder Score, health-related quality of life (EQ-5D-5L), complications, range of movement and strength, revisions and mortality. The between-group difference in the primary outcome will be derived from a constrained longitudinal data analysis model. We will also undertake a full health economic evaluation and conduct qualitative interviews to explore perceptions of acceptability of the two types of TSR and experiences of recovery with a sample of participants.

**Ethics and dissemination:**

Ethics committee approval for this trial was obtained (London - Queen Square Research Ethics Committee, Rec Reference 22/LO/0617) on 4 October 2022. The results of the main trial will be submitted for publication in a peer-reviewed journal and using other professional and media outlets.

**Trial registration number:**

ISRCTN12216466.

STRENGTHS AND LIMITATIONS OF THIS STUDYRAPSODI-UK is a multi-centre, pragmatic, two-arm, parallel, superiority randomised controlled trial with a parallel sister trial being conducted in Australia.This study includes a full health economic evaluation and a nested qualitative interview study of participants’ experiences.There will be a 2-year follow-up and beyond using National Joint Registry (NJR) data linkage for longer term follow-up.There is the potential cross-over of randomised participants from anatomic to reverse Total Shoulder Replacement due to a lack of rotator cuff integrity when assessed intra-operatively.

## Introduction

### Background and rationale

 Osteoarthritis (OA) of the ‘ball’ (humerus) and ‘socket’ (glenoid) joint of the shoulder is common with advancing age. Resulting shoulder pain and disability significantly impact patients’ work, social and domestic activities, contributing to a considerable burden on healthcare systems.^1^ A total shoulder joint replacement (TSR) may be appropriate when other non-surgical options no longer provide adequate pain relief. In 2023, 8821 primary TSRs were performed across England, Wales and Northern Ireland, with 55% of these procedures attributed to shoulder OA.^2^

There are two primary types of TSR: anatomic (aTSR) and reverse (rTSR). Anatomic TSR aims to preserve the natural anatomy of the shoulder joint, making it suitable for patients with an intact rotator cuff and normal functioning shoulder muscles that enable lifting the arm above shoulder height. In contrast, rTSR reverses the orientation of the joint components—placing the ‘ball’ on the glenoid and the ‘socket’ on the humerus—and relies on the deltoid muscle for arm elevation. This approach is often indicated for patients with a deficient or dysfunctional rotator cuff, as it compensates for rotator cuff deficiency. Despite its clinical success, aTSR is associated with subsequent rotator cuff deficiency,^3^ which is one of the leading causes of revision surgery. As a result, more patients with an intact rotator cuff are being treated with rTSR, even in the absence of clear evidence demonstrating its superiority over aTSR. While rTSR is increasingly being performed in clinical practice,^2 4^ there are insufficient data regarding its cost-effectiveness compared with aTSR, particularly in terms of hospital costs. Data from the American healthcare system suggests that there may be higher hospital costs associated with rTSR, making it essential to better understand the relative benefits and economic implications of the two procedures.^5 6^

The current evidence base is limited, with a Cochrane review in 2020 reporting a lack of high-quality randomised controlled trials (RCTs) comparing aTSR and rTSR in patients with shoulder OA and an intact rotator cuff.^7^ Data from the National Joint Registry (NJR)^2^ indicate that the risk of revision of aTSR for cuff failure is 0.42 per 100 prosthesis years compared with rTSR with a rate of 0.02 per 100 prosthesis years. More recently, a Korean group undertook a systematic review and meta-analysis of six retrospective studies of 447 patients with intact rotator cuffs for primary shoulder OA receiving either aTSR or rTSR.^8^ They reported that range of movement (ROM) was better (specifically external rotation, although there was tentative evidence for better ROM in all tested directions) for aTSR compared with rTSR. While function scores were not different, glenoid loosening (the failure of the glenoid component of the prosthesis to remain securely attached to the bone) was more common with aTSR, whereas scapular notching (erosion of the inferior scapular neck due to repetitive mechanical abutment of the humeral component during adduction) only occurred with rTSR. Other surgical risks were similar for the two types of implant, and overall, there was no difference in revision rate. However, the included studies were all retrospective, and many suffered from methodological limitations, including short follow-up and small sample sizes. Therefore, considerable uncertainty remains as to whether rTSR leads to better and more enduring outcomes compared with aTSR in this patient group.

In 2015, the James Lind Alliance priority setting partnership for shoulder surgery identified a comparison of different types of shoulder replacement for shoulder arthritis as a research priority.^9^ A 2020 review commissioned by the National Institute for Health and Care Excellence (NICE) found that no RCTs had compared the clinical or cost-effectiveness of aTSR versus rTSR in patients with shoulder OA and an intact rotator cuff. As a result, NICE recommended an RCT to address this gap in the evidence base.^10^ The RAPSODI-UK trial was designed in response to a commissioned call from the National Institute for Health Research Health Technology Assessment programme for a pragmatic trial to provide the high-quality evidence that has been previously lacking in this area.

The RAPSODI-UK trial will also include a nested qualitative study to explore patient perceptions of acceptability of the interventions, their experiences of recovery and patients’ goals at two postoperative time points (approximately 2 and 12 months after surgery). It is expected that this nested study will provide valuable contextual information to further understand the RCT results.

### Aims and objectives

The overall aim of the RAPSODI-UK RCT is to provide robust evidence that can guide clinical decision-making and inform healthcare policy regarding TSR for shoulder OA in older adults. The specific objectives are listed in box 1.

Box 1Objectives of the RAPSODI-UK trialTo determine whether reverse total shoulder replacement (rTSR) is superior to anatomic total shoulder replacement (aTSR) for the treatment of painful osteoarthritis (OA) of the shoulder joint with an intact rotator cuff and suitable bone stock in patients aged 60 years and over as measured by patient-reported pain and function using the Shoulder Pain and Disability Index (SPADI) at 24 months.To obtain estimates about recruitment rate and assumptions regarding cuff integrity and whether this leads to crossovers from aTSR to rTSR via an 8-month internal pilot.To compare the cost-effectiveness of the two treatment options to determine the most efficient provision of future care and to describe the resource impact on the National Health Service (NHS) for both treatments.To explore patients’ perceptions of acceptability of aTSR and rTSR, patients’ goals, and their experiences of recovery, within and across trial groups.

## Methods

This protocol is reported in line with the Standard Protocol Items: Recommendations for Interventions Trials (SPIRIT)^11^ and the Consolidated Standard of Reporting Trials (CONSORT) guidelines.^12^

### Trial design

RAPSODI-UK is a multi-centre, pragmatic, two-parallel arm, patient and assessor blinded, superiority RCT with internal pilot (see online supplemental file for further details relating to the internal pilot and progression criteria). The participant flowchart can be seen in figure 1.

**Figure 1 F1:**
[figure not shown]
Overview of trial design and flow of participants through the trial.

An accompanying health economic evaluation, and a nested qualitative study with a subset of trial participants will be included.

### Setting

Participants will be recruited from orthopaedic departments of NHS Hospitals in England, Wales and Northern Ireland that routinely treat shoulder OA with both aTSR and rTSR. We will collaborate with approximately 28 high and medium volume hospital sites and will prioritise those that have performed at least 130 TSRs in the 3 years preceding 2019. Linkage to NJR data will be used to compare mortality and revision rates at follow-up points beyond 2 years. Scottish sites will not be included given the need to link data to the NJR dataset.

### Eligibility criteria

Eligibility criteria are presented in box 2.

Box 2Participant eligibility criteria for the RAPSODI-UK trialInclusion criteriaAged 60 years and over.Diagnosis of painful osteoarthritis (OA) of the glenohumeral joint, confirmed by routine radiographs, that has not been controlled by previous interventions.An intact rotator cuff determined by pre-operative advanced imaging (ultrasound, MRI or CT).Minimal glenoid erosion determined by pre-operative CT or other imaging in whom an off-the-shelf replacement is appropriate.Able to give informed consent.Exclusion criteriaShoulder replacement surgery contra-indicated.A diagnosis of inflammatory arthritis, acute trauma or trauma sequelae.Evidence that the patient would be unable to adhere to trial procedures or complete questionnaires.Trial participant for TSR for the opposite shoulder.

### Recruitment

Potential participants will be screened and identified from the waiting lists for TSR prior to the pre-operative clinic, or from those patients attending an outpatient clinic. The research team will work closely with the delegated hospital staff (eg, surgeons, nurses, physiotherapists) at each participating site to optimise the local screening and recruitment processes.

Radiographs (typically anteroposterior and axial views) to confirm OA of the shoulder joint will have been taken as part of routine care. More advanced routine imaging with CT, MRI or ultrasound carried out within 6 months of surgery, where possible, will be used to assess the integrity of the rotator cuff. Earlier scans can be used if scans within 6 months are not available as part of local routine care. A routine CT scan will be used to determine the extent of glenoid erosion.

Delegated hospital staff will screen and approach eligible patients to take part in the trial. For new patients, this will be at their outpatient appointment clinic. For waiting list patients, this may require bringing the patient in for an outpatient appointment or calling the patient and/or posting to them the RAPSODI-UK trial patient information leaflet. Posters about the trial will also be displayed in clinics. Informed consent will be confirmed and baseline data collected when the patient has been confirmed fit for surgery at the pre-operative assessment clinic or consent to surgery clinic by a suitably qualified and delegated member of the research team. Where feasible, this will be done within 6 weeks from the planned surgery.

Consent can occur face-to-face during a clinic appointment or alternatively, can be carried out remotely via phone or video call. Remote consent will be carried out by a GCP-trained staff member and witness. On the remote consent call, the patient will have the option to verbally consent and be posted the baseline forms to complete and return to York Trials Unit via prepaid post. When the patient next comes into the hospital, they will confirm their willingness to participate and physically sign the Verbal Consent Form.

#### Sequence generation and allocation concealment and implementation

Allocation will be 1:1, using random permuted blocks of random block size, stratified by age (60-69; 70+) as a surrogate of deteriorating shoulder rotator cuff function. The allocation schedule will be generated by a trial statistician, otherwise not involved in the recruitment or randomisation of participants. It will be implemented using a secure web-based randomisation service managed by York Trials Unit, ensuring treatment concealment and unbiased allocation. The research team at the site will access the online service to perform the randomisation ideally 2 weeks before surgery but no earlier than the pre-operative clinic to confirm the patient is fit for surgery.

#### Blinding

Participants will be blinded to treatment group allocation and will not be told which TSR type they have received. This is feasible given that the scars of the two TSR types appear the same. Participants will be provided with a card to remind them about their blinding and to remind healthcare professionals at appointments about being blinded. Sites will also be provided with a generic leaflet about helping participants recover from their operation which is not specific to TSR type. To help prevent unblinding of participants from occurring, we will ask sites to list participants as a ‘RAPSODI-UK Total Shoulder Replacement’. If a participant inadvertently becomes unblinded to their allocation, this will be recorded. Surgeons performing the surgery cannot be blinded to allocation. Outcome assessors who will undertake the shoulder ROM and strength of shoulder measurements will be blinded to the replacement type the participant received. Blinded outcome assessors will be asked not to access radiographic records of the participant as these do not form part of the outcome assessment for the patient. The primary outcome is a patient-reported measure (SPADI), helping mitigate surgeon influence. Participants will be informed which type of surgery they had after primary outcome data are collected at 24 months. We will remind site staff on hospital Case Report Forms not to unblind patients and to record if it does happen. Participants will only be unblinded earlier than 24 months if there is deemed to be a clinical need by their surgeon.

Trial participants will also be asked at 24 months whether they have been informed of the type of replacement they have had during the trial, and which type they thought they had received. Participants may, however, request to withdraw from being blinded and be provided with their allocation: any such participants will continue to be followed up, but information on their unblinding will be recorded.

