#### Primary outcome

The primary outcome is the total pain and disability score measured using the SPADI at 24 months. The 13-item SPADI is a validated and sensitive instrument for use in TSR that assesses two domains: pain (five items) and functional activities (eight items) on numerical rating scales.^15 18^ The total score ranges from 0 to 100 where 0 indicates no shoulder pain or disability and 100 indicates worst possible shoulder pain or disability.

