#### Secondary outcomes

Combined pain and disability score: measured via the combined SPADI score at 3, 6, 12 and 18 months, and over 24 months.Individual pain and disability scores: measured via the subscale scores of the SPADI at 3, 6, 12, 18 and 24 months, and over 24 months.Pain and function: measured via the OSS, which is a 12-item patient-reported outcome measure of shoulder pain and function with five response categories and overall scale ranging from 0 (worst) to 48 (best).^19^ The OSS will be collected at 3, 6, 12 and 24 months.Global perceived effect: patient opinion about the change in their shoulder since the start of the trial will be assessed at 24 months via the question “Compared with just before the operation for your shoulder replacement at the start of the study, how would you say that your shoulder is now?”. Responses will be on a 5-point Likert scale with the following options: much improved, improved, same, worse and much worse.^20^Health-related quality of life: measured at 3, 6, 12 and 24 months via the EQ-5D-5L, a validated measure of health-related quality of life in terms of five dimensions (mobility, ability to self-care, ability to undertake usual activities, pain and discomfort, anxiety and depression) each with five levels of severity.^21^ The EQ-5D-5L will be used to calculate quality-adjusted life years (QALYs) according to NICE best practice guidance at the time of the analysis.ROM: The range of shoulder flexion, abduction, internal and external rotation will be assessed by a suitably trained blinded assessor at 24 months using a hand-held goniometer following trial specific instructions and recorded as continuous measurements except for internal rotation that will be assessed according to the position of the thumb to the spine.^22^Strength of shoulder: Shoulder strength will be measured at 24 months using a spring balance as described for the Constant Murley Score by a suitably trained blinded assessor.^22^ This will be done for both shoulders and repeated three times and will only be completed if the arm can be elevated to 90 degrees (abduction). Neither strength nor ROM will be collected during the interim follow-up timepoints given the need for in-person measurements by a trained team member. Both ROM and strength measurements will be collected only at baseline and at 24 months.Complications: Expected complications related to the affected shoulder will be recorded and will include (but are not limited to) deep and superficial wound infection (using Centers for Disease Control and Prevention definition),^23^ re-hospitalisation, and implant, nerve and skin problems. These complications will be recorded at 3, 6, 12 and 24 months. Complications specific to the arthroplasty implant (ie, glenoid loosening (keeled and pegged), scapula notching and lucency of the humeral stem)^24^,^26^ will be reviewed by the local surgeon using post-operative radiographs (typically anteroposterior and axial views) and 2 year radiographs (typically anteroposterior and axial views) or the most recent radiographs if not available at 2 years. This assessment will be performed using routinely taken radiographs and where feasible by a local surgeon who did not operate on the participant. Depending on the availability of funding, these radiographs will be pseudonymised of personal data and collected for central review independent of the surgeons at the local hospital.Re-operations: An operation to correct the complications of a previous operation due to, for example, an infection or dislocation. Re-operations will be recorded at 3, 6, 12 and 24 months.Revision and mortality: Rates of implant revision and patient mortality over the 24-month follow-up will be collected from hospital and the NJR records to identify patients in whom revision was undertaken elsewhere or death that is not recorded in the hospital records. The NJR definition of a revision will be used, which is any operation where one or more components are added to, removed or modified in a joint replacement or if a Debridement And Implant Retention with or without modular exchange is performed.^27^Resource use: Data on healthcare resource use will be collected to inform the economic evaluation (eg, length of hospital stay, re-hospitalisation, physiotherapy). Data will also be recorded about use of private care, days lost to work and normal activities. These data will be collected from participants and hospital records at 3, 6, 12 and 24 months.

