### Data collection

Data will be collected from participants at baseline, 3-, 6-, 12-, 18- and 24-months post-randomisation. There will be a secondary outcome endpoint of 18-month follow-up to collect the SPADI only to try to help maintain trial engagement and reduce missing data of the primary outcome. Baseline data will be collected with participants at recruiting sites by a delegated member of staff, for example, research nurses. Follow-up data collection of the primary outcome and most secondary outcomes will be by postal questionnaire with supplemental telephone/video conference follow-up for non-responders or collected in clinic when attending at these timepoints as part of their routine care. Delegated research staff will also collect data from hospital records at 3, 6, 12 and 24 months. This includes a local assessment of routine post-operative radiographs and those routinely taken at 24 months (or earlier if not routinely available at this timepoint) to assess complications specific to the arthroplasty implant. Final follow-up data collection will include an outpatient clinic attendance at 24 months to assess shoulder ROM and strength by a blinded assessor. All reporting of data collection will be undertaken in line with the CONSORT statement.^12^

To minimise attrition, we will use multiple methods to maintain contact with participants, including full contact details (postal address, mobile phone number and email address if available). For postal data collections, two reminders will be sent to non-responding participants (at 2 and 4 weeks past the due date), with a final attempt to obtain data 6 weeks post-due date. Newsletters will be circulated to participants during the trial to keep them informed and engaged.^40^ Given that the 24-month follow-up clinic is not a routine appointment at all participating hospitals, all trial participants will receive a £20 gift voucher for attending the clinic and as a thank you for completing their follow-up questionnaires.

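### Disclosure of implant type is tied to the 24-month SPADI alone, so some participants may have range of movement and strength measured after learning their implant

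*Protocol article*

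**What the plan says.** All references are to the protocol article.

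- **Disclosure rule (Blinding):** "Participants will be informed which type of surgery they had after primary outcome data are collected at 24 months". The same section limits unblinding before 24 months to clinical need as judged by the surgeon. It also lets a participant ask to leave the blind.
- **Primary outcome:** "The primary outcome is the total pain and disability score measured using the SPADI at 24 months".
- **How the SPADI is collected (Data collection):** "Follow-up data collection of the primary outcome and most secondary outcomes will be by postal questionnaire with supplemental telephone/video conference follow-up for non-responders". As an alternative, participants who have a routine appointment around that time may complete it there.
- **How ROM and strength are collected (Data collection):** "Final follow-up data collection will include an outpatient clinic attendance at 24 months to assess shoulder ROM and strength by a blinded assessor". On the status of that visit, the section says: "Given that the 24-month follow-up clinic is not a routine appointment at all participating hospitals".
- **When ROM and strength are measured (Secondary outcomes):** "Both ROM and strength measurements will be collected only at baseline and at 24 months". Strength is taken with a spring balance, three times on each shoulder.
- **Safeguards:** Trial design describes the trial as blinded for both patients and assessors. Under Blinding, assessors are asked not to look at the radiographic records, and participants carry a card reminding them and their clinicians about the blind.

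**The concern.** The event that permits disclosure is completion of one questionnaire outcome. Two other outcomes that are meant to be measured blind arrive by a different route, and the rule does not mention them. A participant may return the postal SPADI, be told the implant, and then attend clinic for ROM and strength, with no departure from the protocol.

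Two things could follow. A participant who knows the implant may perform differently on a test that depends on effort, as a spring-balance strength test does. The participant may also tell the assessor, which would end the assessor's blind. The 24-month visit is the only post-operative measurement of these outcomes, so no earlier blinded follow-up value could stand in for it. Expectations could also differ by arm: the Introduction cites retrospective evidence of better ROM with the anatomic implant, and the Interventions section credits that implant with the potential for a normal range of function.

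**Working it through.** No figure in the protocol bears directly on this point, so the check sets the passages side by side.

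1. **What releases the allocation?** Collection of the primary outcome at 24 months (Blinding), which is the SPADI total score and nothing else (Primary outcome).
2. **How does the SPADI arrive?** By post as the default, by telephone or video for non-responders, or in clinic for those attending as routine care (Data collection).
3. **How do ROM and strength arrive?** At a 24-month outpatient attendance that is not routine at every hospital (Data collection).
4. **Is the order fixed?** No section puts the clinic attendance before the questionnaire, or makes disclosure wait for the clinic.
5. **Does another safeguard close the gap?** The restriction on early unblinding covers only the time before 24 months, so it does not protect a clinic visit after that point. The instruction on radiographs protects the assessor from one source of information but not from the participant. The card is a reminder and does not delay disclosure.
6. **Which orders are possible?**
   - Clinic before the SPADI, or both at one visit with disclosure afterwards: the blind holds.
   - SPADI first, clinic next, disclosure last: the blind holds.
   - SPADI first, disclosure next, clinic last: the participant's blind is lost before ROM and strength are measured. The rule permits this order.

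**Illustration only.** None of these inputs is a documented value for ROM or strength, except that 182 per group is borrowed from the SPADI sample size. Assume 182 per arm, an unadjusted comparison, no true difference, a share *f* of participants measured after disclosure, and a differential shift of *b* SD among them. The standard error of the difference in SD units is √(2/182) = 0.105 and the bias is *f* × *b*. The resulting two-sided type I error, nominally 5%, is:

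| *f* | *b* | Bias (SD) | Type I error |
|---|---|---|---|
| 0.25 | 0.1 | 0.025 | 5.7% |
| 0.50 | 0.2 | 0.10 | 15.9% |
| 1.00 | 0.2 | 0.20 | 47.9% |

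The effect runs from negligible to large depending on *f* and *b*, and the document gives neither. The table shows why the order matters if both are appreciable; it does not estimate what will happen in this trial.

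**The case against.** The strongest reply is that the rule sets an earliest time, not a schedule. It does not say that participants are told on receipt of the questionnaire, and no section describes disclosure before the clinic visit. The timing of a disclosure letter is also the kind of operational detail a journal article leaves to the full protocol, which is not shown. The first part stands: loss of blinding is permitted, not planned. The second part does not dispose of the point, because the article states the trigger, and the stated trigger covers only one of the outcomes to be measured blind.

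Some stronger readings are tempting but not supported.

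- **That the SPADI and the clinic visit are always separate.** The SPADI may be collected in clinic, so for some participants there may be no interval.
- **That assessors are unblinded by the rule.** Only the participant's blind lapses directly. Assessor unblinding needs a further step, the participant telling the assessor.
- **That postal follow-up running to 6 weeks past the due date shows large exposure.** That delay postpones the SPADI and hence disclosure, which makes the safe order more likely. Exposure needs an early SPADI and a late clinic visit, and the article gives no clinic window.
- **That the 24-month questions on believed allocation are contaminated.** The article does not say on which form or at which visit they are asked. If they are in the same questionnaire as the SPADI, they precede disclosure.
- **That participants will change their effort according to implant.** This is plausible for strength but not documented. The article does not say whether ROM is active or passive.

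**Conclusion.** The point holds as a gap in a stated rule. The trigger for disclosure does not protect the blind for 24-month ROM and strength, so for these secondary outcomes the description of the trial as patient and assessor blinded is not secured. A reader might infer that the main result is at risk, but it is not: under this rule disclosure comes after the SPADI has been collected.

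How many participants would be measured after disclosure, and how far their results would shift, cannot be derived from the document. The conclusion rests on the absence of any stated order between questionnaire, clinic attendance and disclosure. If the full protocol or site instructions already hold disclosure until after the clinic visit, only the article's wording needs correcting. The change is worth making because it is cheap and these outcomes have no other post-operative measurement.

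**What to change.** Replace the disclosure sentence under Blinding with wording to this effect: *participants will be informed of their implant type only after all 24-month data (questionnaire, blinding questions, and clinic ROM and strength) are collected or the 24-month data collection window has closed.* The trials unit should release each disclosure against a check of those items. Leave the clinical-need and participant-request routes to unblinding as they are.

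The cost is one sentence and a database check. Some participants will learn their implant somewhat later. Sample size and analysis do not change.
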